### Exploratory studies

Mechanistic studies: Overall, approximately 2.5 ml of blood will be collected for mechanistic studies in all babies: (i) 1.0 ml will be collected within 0–6 h of age, (ii) 0.5 ml will be collected at 48 (*±* 4) hours of age, and (iii) 1.0 ml will be collected at around 84 (± 4 h) hours of age.Magnetic resonance spectroscopy: In centres with facilities for undertaking proton magnetic spectroscopy using harmonised sequences for quantification of thalamic n-acetyl aspartate (NAA), these sequences will be acquired at the time of routine clinical MR scanning.

## Study management

The day-to-day management of the study will be co-ordinated through the Centre for Perinatal Neuroscience, Imperial College London. The trial management group (TMG) will oversee all aspects of the day-to-day running of the study, and will consist of the investigators, trial manager, trial research fellow and other COMET trial staff based at the Centre for Perinatal Neuroscience, Imperial College London. TMG will hold a monthly teleconference of all COMET investigators for the entire duration of the trial to discuss the data quality and recruitment.

### Data collection tools

Prior to the start of recruitment, a manual of procedures (MOP) will be developed providing details of the protocol design and procedure and definitions of each data variable, and procedures for data lock. All study personnel entering the data (research nurses and site principle investigators) will be trained and certified during site initiation and names will be documented in the delegation log.

### Sample size calculation

The Bayley-IV Cognitive Scale Composite score has a normative mean of 100 and SD of 15. To detect a clinically important minimum difference of 5 points (0.3 SD), at a 0.05 significance level and 90% power, we would need 191 neonates per group, 382 in total. This increases to 426, after allowing for a conservative 10% drop-out rate (Table 2). The total duration of the trial is 66 months which will include a six-month trial set up period, 30 months of recruitment, and outcome assessments at the age of 24 (*±* 2) months.

**Table 2 Tab2:** Sample size calculation

Size of group difference	Total study sample size	
	90% power	80% power
4 points	660	494
5 points	426	318
6 points	296	224
7 points	218	166
8 points	168	128
9 points	134	100
10 points	110	84

The implication of changing the power of the study and the size of outcome differences between groups has been examined and is shown in the subsequent table. This shows the total sample size required in both groups combined, after allowing for a 10% drop-out rate (Table 3).

**Table 3 Tab3:** Effect of drop out on study power

Drop-out rate	Study power
10%	90.0%
12.5%	89.4%
15%	88.5%
17.5%	87.7%
20%	86.5%

The assumed attrition rate of 10% is conservative, as we have consistently obtained > 97% follow up at 18 to 22 months in previous trials performed in the UK. The implications of a higher drop-out rate upon the power of the trial are shown below. If the drop-out rate is 20%, the study would still have an 87% power to detect a 5-point difference between groups.

### Statistics and data analysis

The primary outcome is the Cognitive Scale Composite score from the Bayley-IV examination at 24(*±* 2) months. Based on previous experience the scores are expected to be approximately normally distributed, and thus a two-sample t-test will be used to compare between groups. The mean difference in outcome between groups will be reported, along with a corresponding confidence interval. If the outcome scores are not normally distributed, an appropriate data transformation will be explored, or alternatively a non-parametric test (Mann-Whitney test) may be utilised.

Secondary outcomes are both short term (in hospital) or longer term (at 24 months). Continuous secondary outcomes will be analysed using the unpaired t-test if normally distributed, or the Mann-Whitney otherwise. The Chi-square test or Fisher’s exact test will be used to compare categorical outcomes between groups. For each outcome, a point-estimate of difference between groups will be reported, alongside a corresponding confidence interval.

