## Study design

### Setting

Cooling in mild encephalopathy (COMET) is a phase III multi-centre open label two-arm randomised controlled trial (RCT) with internal pilot and masked outcome assessments. Administration of cooling therapy cannot be masked. The trial will recruit from five neonatal operational delivery networks (ODN) involving around 50 to 60 NHS hospitals. The recruitment will occur at both tertiary and non-tertiary (non-cooling) centres, although the neonates recruited from non-tertiary centres will be transferred to a tertiary centre after randomisation.

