### Randomisation and trial intervention

If the neonate meets the trial inclusion criteria, the availability of a cooling device and intensive care cot space at a cooling centre will be checked before approaching parents for trial participation. Once parental consent is obtained, babies will be randomised to whole-body hypothermia or normothermia within 6 h of birth, using a web-based program developed by Sealed Envelope private limited, London. The randomisation will be performed using minimisation to balance the treatment allocation by site and severity of encephalopathy within mild encephalopathy.

Initial assessment and randomisation (and initiation of whole-body hypothermia or normothermia) will occur at the hospital of birth. The babies in both arms, who are born at a non-cooling centre (Local Neonatal Unit (LNU) or Special Care Baby Unit (SCBU)) will be then transferred to the nearest neonatal intensive care (NICU) cooling centre for continued care.

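### Allocation is minimised on site and severity but the primary analysis is an unadjusted t-test, so its confidence interval is conservative to the extent that those factors predict the cognitive score

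*Protocol article*

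**What the plan says.** On allocation, the protocol article (Randomisation and trial intervention) states: "The randomisation will be performed using minimisation to balance the treatment allocation by site and severity of encephalopathy within mild encephalopathy". Recruitment is from "five neonatal operational delivery networks (ODN) involving around 50 to 60 NHS hospitals" (Setting).

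On analysis, Statistics and data analysis expects approximately normal scores, "thus a two-sample t-test will be used to compare between groups". If the scores are not normal, a transformation is considered, or "alternatively a non-parametric test (Mann-Whitney test) may be utilised". The next paragraph adds: "Continuous secondary outcomes will be analysed using the unpaired t-test if normally distributed, or the Mann-Whitney otherwise". Categorical outcomes get a chi-square or Fisher's exact test.

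No section names a covariate, a stratified test or an adjusted model for any clinical outcome. The only regression is the bivariate cost-and-consequence model in Health economic evaluation. The sample size is likewise an unadjusted comparison: a 5-point difference with a "normative mean of 100 and SD of 15", "at a 0.05 significance level and 90% power".

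**The concern.** Minimisation makes the arms alike on the chosen factors. If those factors predict the outcome, part of the variation that would otherwise move the mean difference by chance has been removed by design. The two-sample t-test does not know this. It treats the arms as independent samples and leaves the factor-related variance in its error term. Its standard error is then larger than the real sampling error, the interval is too wide and the p-value too large.

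At stake are the calibration of the headline interval and some precision that the design has already paid for. Precision has some value here: the protocol's Table 3 shows power falling to 86.5% if drop-out reaches 20%, and adjustment could offset part of such a loss without recruiting more babies. The same mismatch affects the continuous secondary outcomes and the Mann-Whitney fallback.

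**Working it through.** **Inputs from the protocol article.** Difference 5, SD 15, alpha 0.05 (taken as two-sided, which reproduces the stated size), power 90%, 191 per arm, 382 assessed, 426 randomised (Sample size calculation); 50 to 60 hospitals (Setting). **Assumed:** R², the share of score variance explained by severity and site together. The document gives no value, so a range is shown.

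**Step 1: the plan's own figure.** The normal approximation gives n = 2(1.960 + 1.282)² × 15²/5² = 189.1, so 190 per arm. The exact noncentral-t calculation gives 191 per arm, 382 in total. With 10% drop-out, 191/0.9 = 212.2, so 213 per arm and 426 in total. Every row of Table 2 reproduces, and Table 3 reproduces to within 0.3 points. The sample size is sound for the unadjusted test.

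**Step 2: effect of ignoring the balanced factors, if balance is exact.**
- Reported SE = 15√(2/191) = 1.535.
- True SE = 1.535 × √(1 − R²).
- Type I error of the t-test = 2[1 − Φ(1.960/√(1 − R²))].
- Power, unadjusted = Φ[(5/1.535 − 1.960)/√(1 − R²)].
- Power, adjusted = Φ[5/true SE − 1.960].

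At R² = 10%, √0.9 = 0.9487 and the true SE is 1.456. Type I error is 2[1 − Φ(2.066)] = 3.9%. Unadjusted power is Φ(1.368) = 91.4% and adjusted power is Φ(1.474) = 93.0%.

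| Assumed R² | True SE | Reported SE too large by | Type I error | Power, t-test | Power, adjusted |
|---|---|---|---|---|---|
| 0 | 1.53 | 0% | 5.0% | 90.3% | 90.3% |
| 2% | 1.52 | 1.0% | 4.8% | 90.5% | 90.8% |
| 5% | 1.50 | 2.6% | 4.4% | 90.8% | 91.7% |
| 10% | 1.46 | 5.4% | 3.9% | 91.4% | 93.0% |
| 20% | 1.37 | 11.8% | 2.8% | 92.7% | 95.4% |

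Before rounding, the power gain is 0, 0.3, 0.8, 1.5 and 2.7 points.

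**Step 3: does this survive imperfect balance?** With 382 assessed children over, say, 55 hospitals there are 382/55 = 6.9 per hospital, so sites cannot be balanced exactly. Minimisation was simulated with N = 382, 55 sites, two equally likely severity levels, a biased coin of 0.8 and 2,500 replicates per setting. The severity levels and the coin probability are assumptions. The adjusted model here used severity plus **fixed** site effects.

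| Severity R² / site R² | t-test SE: reported | t-test SE: empirical | t-test type I error | Power, t-test | Power, site fixed effects |
|---|---|---|---|---|---|
| 0 / 0 | 1.53 | 1.54 to 1.55 | 0.048 | 89.7% | 88.4% |
| 0.05 / 0.02 | 1.53 | 1.47 to 1.50 | 0.048 | 90.9% | 90.4% |
| 0.10 / 0.05 | 1.53 | 1.41 to 1.48 | 0.043 | 92.5% | 93.3% |
| 0.15 / 0.10 | 1.53 | 1.35 | 0.028 | 92.9% | 95.6% |

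Monte Carlo error is about √(0.05 × 0.95/2,500) = 0.004 on type I error and √(0.9 × 0.1/2,500) = 0.006 on power.

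The direction is confirmed, and the size is smaller than the exact-balance formula gives. At a total R² of 0.15 the formula gives a type I error of 0.034 against 0.043 simulated, and a power gain of 94.2 − 92.0 = 2.2 points against 93.3 − 92.5 = 0.8. When nothing is prognostic, site fixed effects raise the reported SE from 1.534 to 1.573, about 2.5%. The random-intercept model proposed below was not itself simulated.

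**The case against.** The strongest reply is that the size of the problem rests on an R² that the document never gives, and that the protocol offers reasons to expect a low one. Severity is confined to a narrow band: babies with moderate or severe HIE, abnormal aEEG background voltage or aEEG seizures are excluded. One central masked team of 2 to 4 certified examiners assesses every child, so site should carry little assessor variance. Babies born at non-cooling centres are moved after randomisation, so the recruiting site is often not the main place of care. At R² = 0 the t-test is correct as it stands, and at 2% the gain is a few tenths of a point. All this stands. It limits the size and rules out a flat statement that precision is wasted, although choosing severity as a balancing factor suggests that it is thought prognostic.

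A second reply is that covariate adjustment is usually set out in a statistical analysis plan, which is not shown. That lowers certainty. It does not remove the point, because the article names a specific unadjusted test and does not leave the method open.

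A reader might infer more than this: that the primary result would be invalid, the false-positive rate inflated or the trial underpowered. The documents do not support that. The difference in means is unbiased, the type I error is at or below 5%, and by the Step 2 formula the t-test has at least 90% power at every R². Nor does the equivalence at R² = 10% (382/0.9 = 424, about 42 more assessed children) show a shortfall; it only restates the assumed 10%.

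A reader might also extend the point to every secondary outcome. For binary outcomes nothing was quantified. Some may be rare (the protocol expects seizures after 6 h in about 5% of babies), and models with site terms can be unstable there.

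**Conclusion.** The mismatch is stated in the text and is worth correcting: allocation is balanced on two factors that the named primary test ignores. The consequence is a conservative interval and p-value, with no bias and no loss of the planned power. Over an assumed R² of 0 to 20%, the reported standard error is 0 to 12% too large, the type I error lies between 5.0% and 2.8%, and adjustment gains about 0 to 3 power points. The standard-error excess and the adjusted powers are ceilings, because they assume exact balance on both factors and charge nothing for estimating their effects. Confidence is high in the mismatch and its direction, and moderate in its practical size. This is a should-change point about efficiency and alignment with the design; the trial's validity is not threatened.

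**What to change.** Make the primary analysis a linear model of the Bayley-IV cognitive composite on arm, with severity as a fixed effect and site as a random intercept. Report the adjusted mean difference with its 95% CI as the headline. Do not fit 50 to 60 site fixed effects: at about 7 assessed children per hospital they can cost more precision than they recover. Keep the two-sample t-test as a sensitivity analysis.

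Analyse continuous secondary outcomes in the same way. For binary outcomes, adjust at most for severity and only where event counts allow; keep the chi-square or Fisher's exact test for rare events.

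The cost is wording in the analysis section and the matching text of any analysis plan, fixed before outcome data are seen. Both factors are already recorded at randomisation, the target difference stays on the same scale, and the sample size need not change.

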**Methods:**

The COMET trial is a phase III multicentre open label two-arm randomised controlled trial with masked outcome assessments. A total of 426 neonates with mild encephalopathy will be recruited from 50 to 60 NHS hospitals over 2 ½ years following parental consent. The neonates will be randomised to 72 h of whole-body hypothermia (33.5 *±* 0.5 C) or normothermia (37.0 *±* 0.5 C) within six hours or age. Prior to the recruitment front line clinical staff will be trained and certified on expanded modified Sarnat staging for encephalopathy. The neurological assessment of all screened and recruited cases will be video recorded and centrally assessed for quality assurance. If recruitment occurs at a non-cooling centre, neonates in both arms will be transferred to a cooling centre for continued care, after randomisation. All neonates will have continuous amplitude integrated electroencephalography (aEEG) at least for the first 48 h to monitor for seizures. Predefined safety outcomes will be documented, and data collected to assess resource utilization of health care. A central team masked to trial group allocation will assess neurodevelopmental outcomes at 2 years of age. The primary outcome is mean difference in composite cognitive scores on Bayley scales of Infant and Toddler development 4th Edition.

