### Primary outcome

The primary outcome is the mean Cognitive Composite Scale score from the Bayley IV examination at 24 (*±* 2) months of age. The RCTs of hypothermia for moderate or severe encephalopathy have used the composite outcome of death or disability because of high mortality rates, whereas mortality is expected to be low in mild encephalopathy. Therefore, a continuous numerical developmental score among survivors will be more robust to detect treatment effects than categorical outcomes and hence was selected as the primary outcome.

Babies who die (the mortality rate is expected to be less than 1% in mild HIE) or who cannot be assessed with the Bayley-IV due to severe disability (also anticipated to be low in frequency) will be allocated a Cognitive Scale Composite score one point below the basal test score (i.e., score of 54) [31, 32].

If the child is too tired to co-operate with the Bayley assessment at the time of the original appointment, the assessment will be re-scheduled and performed at a place more suitable for the child, for example at home, within the window period of assessment.

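### The primary test may switch, on observed non-normality, to a transformation or Mann-Whitney, so the headline p-value and the reported mean difference could refer to different quantities

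*Protocol article*

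**What the plan says.** The abstract (Methods) states the target: "The primary outcome is mean difference in composite cognitive scores on Bayley scales of Infant and Toddler development 4th Edition". The sample size section uses the same scale: "The Bayley-IV Cognitive Scale Composite score has a normative mean of 100 and SD of 15", and the trial is sized "To detect a clinically important minimum difference of 5 points (0.3 SD), at a 0.05 significance level and 90% power", which gives 191 per group and 426 in total after 10% drop-out.

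Under Statistics and data analysis, approximate normality is expected, a two-sample t-test is planned, and the mean difference with a confidence interval is to be reported. The next sentence covers non-normal scores: "an appropriate data transformation will be explored, or alternatively a non-parametric test (Mann-Whitney test) may be utilised".

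Under Primary outcome, a child who dies, or who cannot be tested because of severe disability, "will be allocated a Cognitive Scale Composite score one point below the basal test score (i.e., score of 54"). Deaths are expected in under 1%. Untestable disability is expected to be infrequent, with no figure. The paragraph before gives as its rationale that "a continuous numerical developmental score among survivors will be more robust" for detecting treatment effects than categorical outcomes.

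**The concern.** The method for the single primary comparison depends on how the outcome data look, and the alternatives have different targets. The t-test addresses the difference in means. Mann-Whitney addresses how often a child in one arm outscores a child in the other. A transformed analysis compares means on another scale, where 5 points has no fixed meaning. If the arms differed by a pure shift, the t-test and Mann-Whitney would point the same way. A block of scores fixed at 54 breaks that pattern whenever its size differs between arms.

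The protocol could therefore yield a p-value for one quantity beside an estimate of another. The 54 rule also exists so that death and severe disability count in the mean. If one arm had more of them, the data would look less normal, and that would favour moving to a test in which each such child is only one low rank.

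**Working it through.** **1. The plan's own figure.** Inputs from the sample size section: difference 5, SD 15, alpha 0.05 (taken as two-sided), power 90%.
- Normal approximation: n = 2 × 15² × (1.960 + 1.282)² / 5² = 189.1, so 190 per group.
- Noncentral t: 190 per group gives 89.99% and 191 gives 90.13%, so 191, as stated.
- 191 / 0.9 = 212.2, so 213 per group and 426 in total, as stated.

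The trial is therefore sized for a t-test on the raw-scale mean difference.

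**2. How far the 54 rule departs from normality.** (100 − 54) / 15 = 3.07 SD below the normative mean. At 1%, about 0.01 × 382 = 3.8 children would score 54.

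**3. How often a normality check would fail.** Assumptions: 191 per arm, scores N(100, 15) limited to 55–145, a share p replaced by 54 in both arms, no treatment effect, and Shapiro-Wilk at 5% on within-arm residuals. The article names no criterion and gives no rate of untestable disability, so Shapiro-Wilk and the 2% row are assumptions.

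| Share at 54 | Normality rejected | t-test type I error |
|---|---|---|
| 0% | 3–4% | 4.8–5.4% |
| 1% | 35–36% | 4.7–5.0% |
| 2% | 79–80% | 4.8–5.1% |

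Ranges are across separate simulation runs. D'Agostino's test rejects less often: 23% at 1% and about 60% at 2%. The t-test stays near 5% throughout, so the switch is not needed for validity.

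**4. An excess of 54s in one arm.** Illustration: 1% v 5%, all other scores N(100, 15) in both arms.
- Mean difference: 0.04 × (100 − 54) = 1.84 points.
- Variance with share p at 54: 225(1 − p) + 46²p(1 − p). This gives 243.7 at 1% and 314.3 at 5%.
- SE = √((243.7 + 314.3) / 191) = 1.71, so z = 1.84 / 1.71 = 1.08 and the t-test is significant in about 19% of trials.
- Mann-Whitney: the probability that a child in the 5% arm outscores one in the 1% arm, counting ties as half, is 0.95 × 0.01 + 0.5 × 0.95 × 0.99 + 0.5 × 0.05 × 0.01 = 0.480.
- Its SE is about √(2 / (12 × 191)) = 0.0295, so z = 0.020 / 0.0295 = 0.68 and it is significant in about 10% of trials.

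Simulation agrees: t-test 18–19%, Mann-Whitney about 10%, with Shapiro-Wilk rejecting in 96% of these trials.

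If the other children in the 5% arm also gain 3 points, the net mean gain is (0.95 × 103 + 0.05 × 54) − (0.99 × 100 + 0.01 × 54) = 1.01 points. Mann-Whitney is then significant in 19–20% of trials and the t-test in 9%, so the ordering reverses.

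**5. The other direction: equal shares of 54 and a 5-point gain in the rest.** At 1%, power is about 87% for the t-test and 87–88% for Mann-Whitney. At 2% it is 82–84% and 85–87%. Check at 2%: mean difference 0.98 × 5 = 4.9, SE = √((262.0 + 271.5) / 191) = 1.67, z = 2.93, power about 83%.

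**The case against.** The strongest reply is that this is a conventional fallback, offered permissively, in a plan that expects near-normal scores and few 54s. Much of that stands, and it rules out several stronger readings.

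- **That the 54 rule makes the switch likely.** The documents do not support this. At about 1%, the ceiling the protocol gives for deaths, an assumed Shapiro-Wilk check fails in well under half of trials. It becomes likely only nearer 2%, a rate the protocol does not give. The criterion may sit in an SAP that is not shown, so its absence is not counted here.
- **That the mean difference is abandoned.** The article still says it will be reported with a confidence interval. The defect is a possible mismatch between test and estimate.
- **That the false-positive rate is materially inflated.** Switching on Shapiro-Wilk keeps type I error at 4.8–5.4%. Even taking the smaller of the t-test and Mann-Whitney p-values gives only about 6–6.6%. Outcome assessors are masked, so the open-label design adds little.
- **That the cost-effectiveness analysis loses its scale.** It has its own regression method on the score and a separate Health Economic Analysis Plan. Nothing carries a transformation over to it.
- **That Mann-Whitney is the weaker test.** With equal shares of 54 it is as powerful or slightly more so. The 1% v 5% contrast is illustrative, and both tests have low power there.
- **That deaths would be hidden.** Mortality is reported as a serious adverse event, and survival without impairment is a secondary outcome.

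What the reply does not answer is that the article states a rule leaving the primary comparison open among methods with different targets, when the planned one is adequate.

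**Conclusion.** The point holds in a limited form. The primary p-value could come from a test of something other than the raw-scale mean difference that the trial defines, powers and promises to report. The rule for 54s raises the chance of this (about 36% at 1% and 80% at 2%, if Shapiro-Wilk were the trigger). An excess of 54s in one arm raises it further, towards a test that weights those children less (about 10% v 18–19% significant in the illustration). The fallback protects nothing, because the t-test holds about 5% at this sample size.

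These sizes rest on normal scores outside the 54 group, the assumed normality check and the assumed shares. The mismatch of targets does not depend on them. What is at stake is interpretation and pre-specification, not error control.

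The survivors wording in the rationale is a minor inconsistency. A reader might infer that deaths are left out of the primary analysis, but the rule that scores them as 54 is explicit and governs.

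**What to change.** For the primary outcome, delete the conditional move to a transformation or Mann-Whitney. State that the primary analysis is the difference in mean cognitive score, with deaths and untestable severe disability at 54, and its confidence interval, by the planned t-test whatever the distribution. A robust or bootstrap interval is optional. Keep Mann-Whitney as a labelled sensitivity analysis. Reword the survivors phrase so that the rationale agrees with the scoring rule.

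The cost is wording only, best done before outcome data are seen, and the sample size is unchanged. The one downside is slightly lower power than Mann-Whitney if 54s are equally frequent in both arms: about 84% v 87% at 2%, with other runs 1 to 2 points lower for both tests.
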